## Introduction

Dental caries is considered a multifactorial dynamic disease, determined by the interaction of biological, behavioral, and psychosocial factors related to the individual's environment [1]. There has been a continuous decline in the caries prevalence and lesions progression in the last decades [2]. However, unequal distribution of the disease burden in the population is still observed, and poorer children with low access to dental services are more affected [3].

Authors have stated that caries risk assessment can prevent the onset of the disease or its evolution and, thus, could contribute to guide public interventions and allocate time and resources to those most needed [4]. In addition to being considered an essential element for management and prevention of dental caries, caries risk assessment, could establish the appropriate follow-up appointments [5–7].

The main goals of caries risk assessment are determining the patient's probability of developing new caries lesions in a given period and the risk of present lesions progressing to more severe stages [5, 6]. There are mainly two ways to assess individual caries risk: (a) simple assessment based on factor’s presence or absence, and (b) assessment by multivariate models, a combination of more than one variable, classifying the patient’s caries risk [6, 8].

Several studies about caries risk assessment with children and adolescents were carried out and are summarized in systematic reviews [8–11]. Most primary studies have cohort design and were conducted to determine isolated variables that would have adequate predictive power for developing new carious lesions [12]. Those were unanimous in stating that the past caries experience is the factor with the strongest association with an increased risk of dental caries. In the cohort study by Hall-Scullin, et al., they show that children who had caries lesions in the primary dentition and those who were caries-free at this stage had very different trajectories in the development of new caries lesions in the permanent dentition; hence the authors suggest different prevention strategies for these two groups of children [12].

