#### Interview, examination procedures, and treatment of participants

The child legal guardian will answer a semi-structured questionnaire regarding data needed for the risk assessment criteria listed in Fig. 2. Demographic and socioeconomic data will be collected, such as: sex, age, income, parents' education, and skin color. In addition to the standard questions aimed at providing comprehensive care to the child, the caregiver will be asked about the diet to identify sugar consumption and oral hygiene (regularity and use of fluoride toothpaste). This interview will address specific questions included in the risk assessment (criteria 8–16) (Fig. 2).

The clinical examination will follow a sequence, initially the absence or presence of: thick dental plaque, areas of plaque stagnation (high biofilm retention), and erupting molars will be evaluated. Afterward, a trained and calibrated evaluator will assess the condition for dental caries according to the WHO criteria through the DMFT/dmft index (decayed, missing, and filled teeth) [16]. Then, a professional toothbrushing will be carried out with fluoride toothpaste, and the same trained and calibrated evaluator will assess caries using the International Caries Detection and Assessment System (ICDAS) index in its simplified form [16]. Caries activity will be analyzed using the visual criteria proposed by the NYVAD System and finally the complementary PUFA/pufa index (pulp involvement, ulceration due to root fragments, fistula and abscess for permanent and primary teeth) [16].

After the interview and clinical examination, the researcher will conduct the caries risk assessment expressed in Fig. 1, using the criteria proposed by Caries Care International 4D [15, 16], together with caries experience in primary and/or permanent dentition. The mother's caries experience will be evaluated using the DMFT index only if the score referring to the mother's exam can change the classification; this will be the last item to be listed [16]. The participant will be classified using both methods: simplified and multivariate, by the same researcher. Only after complete classification they will be randomized into one of the groups and follow the intervention and subsequent clinical procedures according to their group, shown in Fig. 3.

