### Randomization, implementation, and blinding

The randomization strategy used will be in permuted blocks with sizes of 4, 6 and 8 and stratified by age (8 to 9 years; 10 to 11 years) and the child's caries experience (DMFS/dmfs ≤ 4; DMFS/dmfs > 4). First, all participants will be evaluated for caries risk by the two strategies, and then participant randomization will be performed in the same session. The allocation sequence used will be obtained from the website www.sealedenvelope.com, and sealed in sequentially numbered opaque envelopes by a researcher without any contact with the practical research procedures.

Another researcher will be responsible for including the participants. Although the groups to which children will be allocated will not be revealed to children and their parents, due to differences in treatments and mainly different intervals for return visits in the two groups, it is difficult to maintain blinding throughout the study for all participants. Therefore, the outcome assessors at 12 and 24 months will be blinded to groups. The groups will be coded in the data analysis worksheets for blinding those who will carry out the statistical analysis. Breaking blinding will not be allowed under any circumstances for outcome evaluators.

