#### Data analysis

Outcomes will be analyzed as count variables. Shapiro–Wilk normality test will be performed. If it presents normal distribution, to compare the primary outcome between the two groups, Student's t-test will be performed. Regarding secondary outcomes, these will also be analyzed by Student's t-test if they have a normal distribution.

A multivariate analysis using negative binomial regression will also be used to compare groups, adjusting for socioeconomic and demographic variables (gender, age, number of children, family structure, and income). Two-tailed tests will be used for all analyses, and the significance level will be set at 5%.

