There is a consensus that caries experience is the most obvious factor in predicting new caries lesions. Therefore, its application in older children would be indicated. Although it is considered an easy-to-apply and straightforward method, the accuracy of this indicator is still moderate. Thus, age is an essential factor to be considered. In younger children and preschoolers, the presence or absence of caries is not effective, as there was no time for the disease to manifest. In these cases, the multivariate models may have a more suitable predictive value [9]. As it is a very comprehensive guide, the applicability of Caries Care International in clinical practice is very time-consuming and challenging for the clinician to understand. Developing a practical guide considering the relevant risk factors for the specific group of children would be an important contribution.

The motivation for this study is that it would be essential to establish safer and more effective parameters for this theme and test different methods (simplified and multivariate) to understand whether there is a difference between these two approaches. In addition, developing a well-designed randomized clinical trial, considered solid scientific evidence, is necessary to answer this research question relevant to clinical practice, but it still has several gaps.

The new calls of scheduled returns for each group were organized with a flexibility interval of around two months; for the multivariate group, the returns for low-risk patients are six to eight months and high-risk patients three to four months, and for the simplified group patients classified as low risk, returns are from nine to twelve months and high-risk patients from five to six months. It is considered an important alternative that enables the protocol's applicability in various scenarios with different logistics of appointments.

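### The negative binomial model adjusts for age but leaves out baseline caries experience, a stratification factor and the protocol's own strongest predictor, so its standard errors will be somewhat too large (a conservative error)

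*Protocol article*

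**What the plan says.** All references are to the protocol article.

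- **Randomization, implementation, and blinding:** permuted blocks, "stratified by age (8 to 9 years; 10 to 11 years) and the child's caries experience (DMFS/dmfs ≤ 4; DMFS/dmfs > 4").
- **Introduction:** the cited studies agree that "the past caries experience is the factor with the strongest association with an increased risk of dental caries". The **Discussion** repeats it: "There is a consensus that caries experience is the most obvious factor in predicting new caries lesions". It adds that the accuracy of this indicator is only moderate.
- **Data analysis:** two between-arm comparisons are named. The first is conditional: "If it presents normal distribution, to compare the primary outcome between the two groups, Student's t-test will be performed". The second is a negative binomial regression, whose covariates are given by name: "adjusting for socioeconomic and demographic variables (gender, age, number of children, family structure, and income").

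Of the two stratification factors, age is in the covariate list and caries experience is not. No other section adds the caries stratum or the baseline DMFS/dmfs count to any analysis.

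**The concern.** Stratified allocation balances the arms on caries experience, so the part of the outcome variance that caries experience explains no longer contributes to the chance difference between arms. A model without that factor still counts this variance as noise. The reported standard error then exceeds the true sampling variability, confidence intervals are wider than they need be, and a nominal 5% test rejects less than 5% of the time under the null. Part of the precision that stratification bought is lost at the analysis stage.

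This bears on how the trial will be read. The Discussion expects the two methods to give very similar results, and intervals that are wider than necessary rule out fewer important differences when the result is close to null.

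**Working it through.** **Inputs.** From Sample size: means 19 and 14 (difference 5), SDs 15 and 10, two-sided alpha 0.05, power 0.80, 103 per group, 20% loss, 250 in total. The proportion of outcome variance explained by the caries stratum (R²) is not in the documents, so a range is assumed, taken as equal in both arms.

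**1. The plan's own figure.** The variances sum to 15² + 10² = 325, so the root-mean-square SD is √(325/2) = 12.75. The normal formula gives n = (1.960 + 0.842)² × 325 / 5² = 102.04, rounded up to 103 per group. A noncentral t check at 103 gives power 0.800. The stated 103 reproduces, and it is an unadjusted calculation.

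**2. Children expected at analysis.** 250 × 0.8 = 200, or 100 per arm. The usual SE of the difference is √(325/100) = 1.803, and 5/1.803 = 2.774.

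**3. Effect of leaving the stratum out.** Under stratified allocation the true variance of the difference is 325(1 − R²)/n, while the unadjusted analysis reports 325/n. Hence:

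- reported SE / true SE = 1/√(1 − R²)
- true type I error = 2[1 − Φ(1.96/√(1 − R²))]
- power without the stratum = Φ[(2.774 − 1.96)/√(1 − R²)]
- power with the stratum = Φ[2.774/√(1 − R²) − 1.96]

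At 100 per arm:

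| Assumed R² | SE ratio | True type I error | Power without stratum | Power with stratum | Gain (points) |
|---|---|---|---|---|---|
| 0.05 | 1.03 | 4.4% | 79.8% | 81.2% | 1.4 |
| 0.10 | 1.05 | 3.9% | 80.4% | 83.2% | 2.8 |
| 0.25 | 1.15 | 2.4% | 82.6% | 89.3% | 6.7 |

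Both power columns use the same R². The 79.2% obtained at R² = 0 is not the right comparator, because stratification has already made the unadjusted estimate more precise when R² > 0.

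**4. Against the planned power.** At 103 per group, power without the stratum is 81.0% (R² = 0.05) and 81.6% (R² = 0.10), so it does not fall below 80%. The 79.8% in the first row above comes from having 100 rather than 103 per arm.

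**5. Check in the planned model.** The formulas above are normal-theory, so a negative binomial simulation was run: 100 per arm, 600 replicates, control mean 19 and SD 15, two equal strata (assumed), no other covariates.

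| High-to-low stratum mean ratio (assumed) | Type I error without / with stratum | Power without / with stratum |
|---|---|---|
| 1.5 | 5.8% / 6.3% | 81% / 83% |
| 2 | 3.0% / 4.8% | 81% / 86% |
| 3 | 1.2% / 4.0% | 84% / 96% |

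Under the null at ratio 2, the model without the stratum reported a mean SE of 0.107 against an actual SD of the estimates of 0.097. The Monte Carlo error on a 5% rate is about √(0.05 × 0.95/600) = 0.9 points, so the ratio 1.5 row shows no detectable difference in type I error. Direction and rough size agree with step 3.

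**6. How large R² might be.** With a share p of children in the high stratum, R² = p(1 − p)(high mean − low mean)²/225 for the control arm. At a mean ratio of 2 (assumed):

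- p = 0.5: means 12.7 and 25.3, R² ≈ 0.18
- p = 0.8: means 10.6 and 21.1, R² ≈ 0.08
- p = 0.9: means 10 and 20, R² = 0.09 × 100/225 = 0.04

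The Discussion describes a sample with high present or past caries experience, so an uneven split at 4 surfaces is plausible and the lower values cannot be excluded.

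**The case against.** The case against has several parts.

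- **The error is on the safe side.** This stands. There is no bias and no excess of false positives. A reader might infer from standard errors that are wrong that the trial's conclusions are at risk of spurious significance; nothing in the documents supports that.
- **The planned power is intact.** This also stands. A reader might infer that the trial becomes underpowered, but 103 per group was computed without adjustment, so the loss is only relative to a better model.
- **The size rests on an assumed R².** This stands, and it is why a range is shown. The Discussion itself calls the predictor's accuracy moderate.
- **One stratification factor is already adjusted for.** This stands: age is in the list, and the omission concerns caries experience only.
- **The covariates may be settled in a separate analysis plan.** This does not remove the point. The article is not silent; it names its covariates and confines them to socioeconomic and demographic variables, so the text as written excludes caries experience.

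A reader might also infer that number of children and family structure will not be collected, since the interview section does not name them. That does not follow. The sentence runs "Demographic and socioeconomic data will be collected, such as: sex, age, income" and so on; its list is introduced as examples, and the questionnaire is semi-structured.

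**Conclusion.** The point holds as a modest, conservative loss of efficiency caused by one omitted covariate. That the list omits a stratification factor which the protocol itself ranks as the strongest predictor is plain from the text. The direction follows from the design: standard errors too large, intervals too wide, tests below their nominal level.

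The size is conditional on R². For R² of 0.10 to 0.25, intervals are about 5% to 15% too wide, type I error is about 3.9% to 2.4%, and about 3 to 7 points of power are forgone at 100 per arm. At R² near 0.05 only 1 to 2 points are forgone. It is worth correcting because the correction costs almost nothing, not because the trial's validity is threatened.

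**What to change.** In Data analysis, add baseline caries experience to the negative binomial model alongside age, either as the randomisation stratum (DMFS/dmfs ≤ 4 or > 4) or as the baseline DMFS/dmfs count. State that this adjusted model provides the between-arm comparison. If the strata turn out lopsided, the count may carry more information than the two-level stratum; the choice should be fixed before outcome data are examined.

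The cost is one sentence. Baseline caries experience is measured before allocation and is needed to randomise each child, so no new data are required. The Study status section reports the trial as suspended and possibly to resume, which leaves room to amend the text before outcomes are analysed.

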### Monitoring

#### Data monitoring

Data collection, management, control and analysis will be undertaken independently by [name].

#### Harms

Possible adverse effects are inherent to dental treatments in general and are already managed by the care unit as a clinical routine. Therefore, the study does not pose a risk to the oral health of participants. If any harm related to the proposed intervention in one of the groups is clearly detected, the study may be suspended and participants will receive the best option of intervention available.

#### Auditing

The data entered will be managed by the study authors. Data will be reviewed periodically. Inconsistencies will be checked, corrected, and recorded.

### Ethics and dissemination

#### Research ethics approval

This study was submitted and approved by the Research Ethics Committee of the Dental School, Federal University of Pelotas (UFPel) (#3.282.962).

#### Consent and assent

Patients will be duly authorized by the guardians, through informed consent and the consent of the child.

#### Confidentiality

Identification numbers will be used to guarantee the participant's confidentiality during data analysis. In addition, participant files will be stored in a secure location.

#### Availability of data

The study data used will be available from the corresponding author ([name]) upon reasonable request.

#### Ancillary care and post-research

Participants will receive dental treatment during and after the end of the study.

#### Dissemination policy

The results will be reported in full through national and international journals, websites, and patient newsletters. As well as disseminating the results to public bodies, to eventually guide public policies and/or inclusion in guidelines.

## Discussion

The risk assessment for dental caries is still a challenge for Dentistry. It becomes even more complex in Pediatric Dentistry, as the child is in constant growth and development. The lack of well-designed studies leads to a series of caries risk proposals, based on one or several criteria, with different assessment systems. This heterogeneity of methods confuses dental professionals and makes the decision-making process difficult.

It is known that the dynamic and multifactorial process of caries disease has led researchers to consider important the risk assessment by multivariate methods, whether in the paper form model or computerized assessment. Standard tools are Cariogram, ADA, CAMBRA, and ICCMS™; many uses three or more caries risk categories. The Cariogram, an open-access software that refers to the probability of developing new caries lesions was used in the majority of well-designed studies. Still, the program's accuracy for children is limited, and its applicability becomes dependent on the use of computers, which is not a reality in different populations, making its generalization restricted [8].

The *Caries Care International* was developed to promote a patient-centered risk-based approach to dental caries management designed for the clinical dental practice, shares the same goals as the ICCMS™ system intended to help patients and dentists control the caries process and maintain health [15]. The four interlinked steps in the cycle all start with a 'D': 1st D: Determine the risk of caries; 2nd D: Detect injuries, scale their severity and assess their activity status; 3rd D: Decide on the most appropriate care plan for the patient at that time; 4th D: Do—implementation of the treatment plan always seeking to preserve the dental structure and control of the patient. Therefore, they are referred to in Caries Care International as the four Ds. Caries risk assessment is the essential first step in the 4D cycle, personalized method that features two risk categories, low risk and high risk [16].

There is a consensus that caries experience is the most obvious factor in predicting new caries lesions. Therefore, its application in older children would be indicated. Although it is considered an easy-to-apply and straightforward method, the accuracy of this indicator is still moderate. Thus, age is an essential factor to be considered. In younger children and preschoolers, the presence or absence of caries is not effective, as there was no time for the disease to manifest. In these cases, the multivariate models may have a more suitable predictive value [9]. As it is a very comprehensive guide, the applicability of Caries Care International in clinical practice is very time-consuming and challenging for the clinician to understand. Developing a practical guide considering the relevant risk factors for the specific group of children would be an important contribution.

The motivation for this study is that it would be essential to establish safer and more effective parameters for this theme and test different methods (simplified and multivariate) to understand whether there is a difference between these two approaches. In addition, developing a well-designed randomized clinical trial, considered solid scientific evidence, is necessary to answer this research question relevant to clinical practice, but it still has several gaps.

The new calls of scheduled returns for each group were organized with a flexibility interval of around two months; for the multivariate group, the returns for low-risk patients are six to eight months and high-risk patients three to four months, and for the simplified group patients classified as low risk, returns are from nine to twelve months and high-risk patients from five to six months. It is considered an important alternative that enables the protocol's applicability in various scenarios with different logistics of appointments.

Among the limitations of this study, we highlight the sample, a restricted population with specific characteristics, high present or past experience of caries, who seek care or are referred to the service that is a reference in clinical pediatric care in the locality. Although the treatments will be carried out in the same place, a clinical unit, the contamination of information and experiences can be a reality among the patients' families. Nevertheless, it is believed that these possible limitations do not directly interfere with the course of the study, being moderated by the coordinating team of the study.

The hypothesis is that both methods present very similar and coincident results. Thus, parameters such as the patient's and dentist's vision, workplace setting can be decisive in the choice, the clinician could choose the one that best suits their practice and is readily applicable to their reality and that of his patient.

### Study status

Suspended: Study halted prematurely because of 2019 Novel Coronavirus (COVID-19) pandemic but potentially will resume.

## Data Availability

The datasets of the study may be obtained from corresponding author upon reasonable request, as long as it does not violate patient confidentiality.

## Abbreviations

CARDEC: Caries detection in children
DMFT/dmft: Decayed, missing, filled, permanent or deciduous teeth
SPIRIT: Standard protocol items for clinical trials
UFPEL: Federal University of Pelotas
WHO: World Health Organization
FDI: World Dental Dederation
ICCMS: International Caries Classification and Management System
ICDAS: Caries Detection and Assessment System
PUFA: Pulp involvement, ulceration due to root fragments, fistula and abscess for permanent and primary teeth
CPQ: Child Perceptions Questionnaire
